### Participants

#### Young People

A total of 50 participants will be recruited on a rolling basis over 6 months from the commencement of the study. Any young person meeting the inclusion criteria listed below irrespective of their gender, ethnicity, religion, education, and disability status will be eligible for inclusion:

If aged ≥17 years and eligible for transition from an adolescent secure hospital, including those experiencing delayed transitions;If formally diagnosed with a mental disorder, and/or learning disability, and/or neurodevelopmental problem.

Any young person meeting the following criteria will be not eligible for inclusion:

If presenting with moderate intellectual impairment with an IQ<65;If in an acute phase of severe mental illness;Cannot provide consent due to physical disabilities and/or language problems or any other neurodevelopmental deficits.

#### Parents/Carers

A total of 20 parents/carers will be recruited pre-, during, and posttransition. Family therapists, responsible clinicians, and social workers from participating adolescent secure services will facilitate this process. A random sample of parents/carers will be interviewed at T1 and T2.

#### Health Care Staff

A total of 30 multidisciplinary team members will be sought for recruitment during the different phases of the study. Key workers involved in the transition planning, such as responsible clinicians, psychologists, family therapists, occupational therapists, social workers, nurses, and health care support workers, will be recruited. A random sample of health care staff will be interviewed postintervention delivery at T1.

### Recruitment and Support

The research team will be informed by health care staff at each site about the young people’s eligibility and capacity to provide written informed consent. The local collaborator will introduce the study to all eligible young people with the help of a study leaflet, a visit or virtual meeting by the research team (to account for COVID-19), and posters advertised at each site. The information leaflets will consider young people’s developmental, language, and learning impairments. The “Bonding Plan,” which was adopted by the MILESTONE study (the largest European transition trial) will be used as a retention strategy with some minor adjustments depending on the setting. For young people in the community, gift vouchers will be provided. For those in secure hospitals, a voucher will be transferred to their account so that they can use it once they are released. Figure 2 presents more details.

**Figure 2 figure2:**
[figure not shown]
Diagram of the feasibility cluster randomized controlled trial. TAU: treatment as usual.

### Sample Size

An intraclass correlation (ICC) coefficient will be calculated to inform the power of the sample size for a further large-scale trial. A statistician based at the joint Faculty of Health, Social Care and Education at Kingston University and St George’s University of London will be involved in the design of the feasibility cRCT. This feasibility study aims to estimate the required sample size for a definitive cRCT evaluation of the intervention. We will estimate the variability in the likely definitive trial outcome (improved mental health and adjustment to adult settings upon follow-up) using an ICC. The sample size of young people may vary between 40 to 60 (8 to 10 young people at each site) and parents/carers 20 to 30 (4 to 5 parents/carers at each site) as recommended [20]. With a sample size of 50, we will be able to estimate a dropout rate of 80% (95% CI –11% to 11%).

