### Allocation Strategy

The adolescent secure service is the unit of randomization and will be randomly selected until 6 sites are recruited. Sites were eligible if they provided low or medium secure care, or they were classified as PICUs. Six adolescent secure hospitals will be randomly allocated into 1 of 3 arms in a 1:1:1 ratio, stratified by area (south versus north) and type (medium versus low versus PICUs) first. Then participants at each site will be allocated to the same treatment. A total of 4 secure units will be allocated to the intervention arms and 2 units allocated to the control arm. Allocation will be performed (computer-generated allocation) by an independent member of the team who will be blind to the identity of the unit. Considering the nature of the intervention, young people and health care staff will not be blinded. The statistician and all team members collecting follow-up data, apart from the principal researcher and fieldworkers, will remain blind to the allocation of the units to trial arms.

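### The lower limits of both sample-size ranges do not follow from six sites: 8 to 10 young people per site is 48 to 60, and 4 to 5 parents/carers per site is 24 to 30

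*Protocol article*

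**What the plan says.** The Allocation Strategy section fixes the number of clusters: "The adolescent secure service is the unit of randomization and will be randomly selected until 6 sites are recruited". The Abstract, the Aims and Objectives and the Feasibility Trial Design section also give six. The six are split 1:1:1 over three arms, so two sites per arm.

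The Sample Size section gives a total and a per-site range in one sentence. For young people the number "may vary between 40 to 60 (8 to 10 young people at each site"). For the other group it is "parents/carers 20 to 30 (4 to 5 parents/carers at each site").

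The Participants section gives single numbers. For young people: "A total of 50 participants will be recruited on a rolling basis over 6 months". For parents/carers: "A total of 20 parents/carers will be recruited pre-, during, and posttransition". It does not say at which sites the parents/carers are recruited. Under Trial Conditions, parents/carers take part in the workshops only in condition 2, and the T1 and T2 descriptions also attach them to condition 2.

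The first item under Progression Criteria and Feasibility Outcomes asks for recruitment of at least 80% of target. It gives no number and does not say whose recruitment is counted.

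**The concern.** A total and a per-site range in the same sentence should be linked by the number of sites. Here they are not, at the lower end of either range. In a feasibility cluster trial, the number of clusters and the cluster size are the basic design figures. This trial will use its clusters to estimate between-cluster and within-cluster variance and an intraclass correlation for the definitive trial. A reader cannot tell whether a site is expected to supply at least 8 young people or may supply between 6 and 7, nor what is expected of each site for parents/carers. Recruitment is also a stop/amend/go criterion, so the numbers behind it should agree wherever they appear.

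**Working it through.** **Inputs.** Sites: 6 (Allocation Strategy). Young people: 40 to 60 in total, 8 to 10 per site (Sample Size). Parents/carers: 20 to 30 in total, 4 to 5 per site (Sample Size). Recruitment numbers: 50 young people and 20 parents/carers (Participants). Criterion: 80% of target (Progression Criteria).

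**Step 1: try to reproduce the ranges.** Total = sites × number per site.

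| Sites | Young people at 8 to 10 | Parents/carers at 4 to 5 |
|---|---|---|
| 4 | 32 to 40 | 16 to 20 |
| 5 | 40 to 50 | 20 to 25 |
| **6** | **48 to 60** | **24 to 30** |
| 7 | 56 to 70 | 28 to 35 |
| Stated | 40 to 60 | 20 to 30 |

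At six sites the upper limits (60 and 30) reproduce, and the lower limits (40 and 20) do not. Five sites give the lower limits, but then the upper limits are 50 and 25. None of these site counts gives either full range. The gaps of 8 young people and 4 parents/carers are too large for rounding.

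**Step 2: work back from the totals at six sites.**
- 40 / 6 = 6.7 young people per site, below the minimum of 8.
- 50 / 6 = 8.3, inside 8 to 10.
- 60 / 6 = 10.
- 20 / 6 = 3.3 parents/carers per site, below the minimum of 4.
- 30 / 6 = 5.

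So the planned 50 young people fit the per-site range, and the planned 20 parents/carers do not.

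**Step 3: the other reading for parents/carers.** If only condition 2 sites recruit them, there are 6 / 3 = 2 such sites. Then 2 × 4 = 8 and 2 × 5 = 10, so 4 to 5 per site gives 8 to 10 in total. Conversely, 20 from two sites is 10 per site. The total of 20 fits 4 to 5 per site on neither reading.

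**Step 4: the recruitment criterion.** 0.80 × 50 = 40 young people. If the 20 parents/carers are also a target, 0.80 × 20 = 16.

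**Step 5: is the precision statement touched?** Half-width = 1.96 × √(0.80 × 0.20 / 50) = 0.111, which is the stated 11 points. The figure is given for a sample of 50 and reproduces there.

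**The case against.** The strongest reply is that little depends on the slip. The number to be recruited is stated once, as 50 young people. The precision statement uses the same 50, and the range is only said to be one within which the sample may vary. That is right, and it limits the point. The 40 to 60 might also have been set as 50 plus or minus 10, or from five sites at the minimum to six at the maximum, as an allowance for losing a site. The document states neither, and neither would make 8 to 10 per site correct at six sites. The ranges are attributed to a cited recommendation that is not at hand. Whatever it says, total and per-site figures in one sentence still have to agree. Condensing a protocol into an article does not explain the mismatch either.

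A reader might go further and infer three things that the document does not support:
- **That the recruitment criterion has no single cut-off.** The range is nowhere called the target. With 50 stated as the number to recruit, the natural cut-off is 40 young people. Examples in which one result passes against 40 and fails against 50 or 60 depend on treating an end of the range as the target.
- **That the target could be picked once the data are in.** The Progression Criteria section says the criteria are to be discussed a priori with the advisory groups, local collaborators and mentors.
- **That the 11-point precision is affected.** It is tied explicitly to 50 and is correct there.

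**Conclusion.** The arithmetic error stands. With six sites, the lower limits should be 48 young people and 24 parents/carers if the per-site figures are right. If the totals are right, the per-site figures should start at about 6.7 and 3.3. The total of 20 parents/carers is 4 below the six-site minimum and twice the upper limit of 10 for two sites. This rests only on the stated count of six sites and, for the two-site reading, on the 1:1:1 allocation.

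The consequence is modest. The planned 50 young people are consistent with 8 to 10 per site, and the natural recruitment cut-off is 40. What stays open is whether parents/carers count towards the recruitment criterion and which sites recruit them. The figures are wrong as written, describe cluster size in a cluster trial and are cheap to correct, so they should be corrected.

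**What to change.** 1. **Sample Size.** Make totals and per-site figures agree, in one of two ways. Either restate the totals as 48 to 60 young people and 24 to 30 parents/carers at six sites, or keep the totals and restate the per-site figures as averages of about 7 to 10 young people and about 3 to 5 parents/carers (from 6.7 and 3.3, rounded).
2. **Parents/Carers.** Reconcile the total of 20 with the Sample Size section, and state whether all six sites or only the condition 2 sites recruit parents/carers. If only the latter, the per-site figure must be rewritten to fit whatever total is intended.
3. **Progression Criteria and Feasibility Outcomes.** Write the recruitment criterion as a count: at least 40 of 50 young people. Say whether parents/carers are counted; if so, 80% of 20 is 16.

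The cost is a few corrected figures in three sections. Restating the per-site figures leaves planned enrolment unchanged. Restating the totals raises the lower limit for young people from 40 to 48, still below the planned 50, and requires at least 4 more parents/carers than the 20 now planned.

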**Results:**

A total of 13 young people and 17 staff members have contributed to the intervention design through online advisory groups on the design of the study and important themes for transition. We have also consulted members of the public (a steering group) including 2 young people who have transitioned to the community and 2 parents/carers. Common identified themes included appropriateness of module content and support during delayed transitions. The content of the intervention will be finalized during the first 6 months of the study. Participants will be recruited over the course of 6 months. An intraclass correlation coefficient will be calculated to inform the power of the sample size for a further large-scale trial. With a sample size of 50, we will be able to estimate a dropout rate of 80% (95% CI –11% to 11%).

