#### Quantitative Analysis

Demographic characteristics will be summarized using descriptive statistics. The between-cluster and within-cluster variance will be determined. Sample sizes for a future definitive trial will be based on detecting a difference in outcomes (mental health and risk presentation) between trial arms, estimated using the TROM and based on combinations of different alpha (ie, significance level) and beta (ie, power) rates. The ICC will be calculated using the linear mixed model and will explore correlations between participants within the same cluster, as well as to inform sample size calculation for the definitive trial.

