### Progression Criteria and Feasibility Outcomes

A traffic light approach (stop-amend-go/red-amber-green) will be used and discussed a priori with PPI, advisory and local collaborators/key contacts, and research mentors about the following criteria:

Recruitment: at least 80% of targetIntervention fidelity: at least 80% of intervention workshops meet the fidelity criteriaIntervention acceptability: at least 80% of staff can be trained and deliver the intervention (barriers and facilitators to intervention design)Follow-up numbers: at least 70% at T1 and 60% at T2Acceptability of assessment tools: at least 70% at T1 and 60% at T2

The outputs are as follows:

Design a multicenter intervention for young people in transition;Design training manuals/toolkit for the health care staff involved in transition;Reflect on good practices across adolescent secure hospitals for transition to adult services and the community and management;Promote co-design and coproduction of evidence-based research.

The impact is as follows:

Design of the future cRCT will promote effectiveness and cost-effectiveness;Assess barriers and facilitators to providing the proposed intervention;Help services to reflect on quality of care and performance pre- and postdischarge;Enable young people to voice their experiences and be dynamically involved in their care.

Figure 3 presents the outcomes for the full-scale trial.

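### The article's only precision statement is wrong as written: an 80% dropout contradicts its own follow-up criteria, and a ±11-point margin that takes participants as independent is printed as a 95% CI

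*Protocol article*

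**What the plan says.** The Sample Size section of the Protocol article states: "With a sample size of 50, we will be able to estimate a dropout rate of 80" per cent, followed in brackets by a 95% CI running from minus 11% to plus 11%. The Results paragraph of the abstract repeats it: "With a sample size of 50, we will be able to estimate a dropout rate of 80% (95% CI –11% to 11" per cent. The article contains no other precision or power calculation.

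Four other places bear on the sentence:

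- **Recruitment target** (Participants, Young People): "A total of 50 participants will be recruited on a rolling basis over 6 months from the commencement of the study". The Sample Size section also allows a range, citing a published recommendation: "The sample size of young people may vary between 40 to 60 (8 to 10 young people at each site").
- **Follow-up criterion** (Progression Criteria and Feasibility Outcomes): "at least 70% at T1 and 60% at T2", one of five criteria under a stop-amend-go approach.
- **Clusters** (Allocation Strategy): "The adolescent secure service is the unit of randomization", and "Six adolescent secure hospitals will be randomly allocated into 1 of 3 arms in a 1:1:1 ratio".
- **ICC** (Quantitative Analysis): "The ICC will be calculated using the linear mixed model and will explore correlations between participants within the same cluster". No value is given for any ICC, and no design effect appears beside the 11% figure.

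**The concern.** The sentence fails in two ways that need no assumption. Read literally, it anticipates a dropout at which the study would miss its own follow-up criterion by a wide margin. It also attaches to 80% an interval that lies nowhere near 80% and allows a negative proportion.

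A third point is one of degree. The margin behind the sentence is what 50 independent people would give, but these 50 are to come from six secure services. If dropout tends to run together within a service, the true margin is wider.

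Retention is one of the quantities this feasibility study exists to estimate, and it feeds a progression criterion. A reader cannot learn from the printed sentence how well it will be estimated. If the rate were carried into planning of the definitive trial as printed, the recruitment inflation would be 1/0.2 = 5-fold; with 20% dropout it would be 1/0.8 = 1.25-fold.

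**Working it through.** **Inputs from the article.** n = 50 young people; stated rate 80%; stated limits –11% and 11%; six sites, so a mean of 50/6 = 8.33 per site; follow-up criteria 70% (T1) and 60% (T2), taken here as percentages of the 50 recruited. **Assumed:** an ICC for dropout, because the article gives none; 0.02 to 0.10 is shown.

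**Step 1. Reproduce the 11.** The normal-approximation (Wald) half-width for one proportion is 1.96 × √(p(1 − p)/n). With p = 0.80 and n = 50:

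1.96 × √(0.16/50) = 1.96 × 0.0566 = 0.111, or 11.1 percentage points.

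The stated 11 is therefore correct as a margin of error for 50 independent participants. Since p(1 − p) = 0.16 at both 0.80 and 0.20, the same margin applies to 80% retention and to 80% dropout and cannot show which was meant.

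**Step 2. The interval that belongs to it.** Around 80% with n = 50:

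- Wald: 80 ± 11.1, so 68.9% to 91.1%
- Wilson: 67.0% to 88.8%
- Clopper-Pearson: 66.3% to 90.0%

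Expressed as a dropout of 20%, the Wald interval is 8.9% to 31.1%. None of these methods gives –11% to 11%.

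**Step 3. Compare the rate with the progression criteria.**

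- 80% dropout: 0.20 × 50 = 10 followed up.
- T1 criterion: 0.70 × 50 = 35 followed up, so at most 30% lost.
- T2 criterion: 0.60 × 50 = 30 followed up, so at most 40% lost.

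**Step 4. Allow for clustering.** The half-width is multiplied by √DEFF, where DEFF = 1 + (8.33 − 1) × ICC. Half-widths in percentage points:

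| Assumed ICC | DEFF | Retention 80% | Retention 70% | Retention 60% |
|---|---|---|---|---|
| 0 | 1.00 | 11.1 | 12.7 | 13.6 |
| 0.02 | 1.15 | 11.9 | 13.6 | 14.5 |
| 0.05 | 1.37 | 13.0 | 14.8 | 15.9 |
| 0.10 | 1.73 | 14.6 | 16.7 | 17.9 |

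The printed 11 corresponds to the first row, a design effect of exactly 1.

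**The case against.** The strongest defence is that this is a slip of wording. The number 11 is arithmetically right as a simple binomial margin, and most readers will guess that 80% retention with ±11 points was meant. No allocation rule, outcome, analysis model or progression threshold depends on the sentence. That is fair as to consequences. It does not make the printed rate or interval correct, and the same wording in two places makes a PDF-reading error unlikely.

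Several stronger readings are tempting, and the article does not support them:

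- **That 80% must mean retention.** This is the likely reading, but it is an inference. The article nowhere states 80% retention or 20% dropout, and the margin is the same for both.
- **That this sentence is the sole basis for 50 participants.** It is the only precision calculation, but the section also gives a recommended range of 40 to 60, and 50 is its midpoint.
- **That the error decides whether a full trial goes ahead.** Follow-up is one of five criteria, and the thresholds are plain percentages with no confidence interval in the rule.
- **That the clustered margins are the true precision.** The planned ICC serves the definitive trial's outcome, not dropout. A wider margin rests on an assumed positive ICC for dropout, and at 0.05 the change at 80% is about 2 points (11.1 to 13.0).
- **That precision had to be stated at 70% and 60%.** Quoting it at one anticipated rate is a legitimate choice. Without clustering, the difference is 1.6 to 2.5 points.
- **That the article omits a cluster-adjusted analysis of retention.** Such detail commonly sits in the full protocol or analysis plan, so its absence here is not a fault.

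**Conclusion.** The point holds in this form: the precision sentence is wrong in both places where it appears. The rate conflicts with the follow-up criteria (10 of 50 followed up, against 35 and 30), and the interval is a ±11-point margin presented as a confidence interval. Both conclusions follow from the article's own figures, with the criteria read as percentages of the 50 recruited. With 80% as the rate and independent participants, the interval is about 69% to 91%.

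It also holds that the ±11 points take participants as independent although recruitment is in six randomized sites. The size of that effect is not known from the article. For an assumed ICC of 0.02 to 0.10 and about 8 participants per site, the margin at 80% would be about ±12 to ±15 points.

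This is a stated figure to be corrected. It does not show that 50 participants are too few.

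**What to change.** The sponsor should first confirm which rate was intended, most likely 80% retention (20% dropout). The sentence should then be replaced in both the Sample Size section and the abstract's Results paragraph. If that rate is confirmed, suitable wording would be:

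*With 50 young people, a retention of 80% (dropout 20%) would be estimated with a 95% CI of about 69% to 91% (±11 percentage points) if clustering is ignored; allowing for clustering in six sites of about 8, the margin would be about ±12 to ±15 points for an assumed ICC of 0.02 to 0.10.*

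The unclustered figure comes first because it rests only on documented inputs, and the clustered range is labelled as an assumption.

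Optionally, add the margins at the progression thresholds: ±12.7 points at 70% and ±13.6 at 60% without clustering, or about ±15 and ±16 at an assumed ICC of 0.05.

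The cost is one sentence reworded in two places and a slightly less favourable stated precision. No extra participants are needed, and no threshold changes.

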### Primary Outcome Measures for a Future Trial to Measure Improved Mental Health, Social Functioning, Adjustment, and Quality of Life

The suitability and acceptability of assessment tools will be based on feedback from the steering and stakeholder groups and key workers in secure hospitals a priori and ad hoc and response rates. Additional feedback will be sought from the participants after completion of the following questionnaires:

Transition Readiness Assessment Questionnaire (TRAQ) [21] (T0, T1, T2): to measure whether the transition intervention outcomes are linked to transition readiness predischarge;Transition Related Outcome Measure (TROM) [22] questionnaire (T1, T2): to measure whether transition outcomes have improved as a result of the intervention;Adult functioning assessed by the Specific Levels of Functioning Scale (SLOF) [23] (T0, T2): to measure social functioning and evaluate how the intervention has facilitated self-management and efficacy in young people;Subjective well-being assessed by the Personal Adjustment and Role Skills Scale (PARS-III) [24] (T1, T2): to measure psychosocial adjustment–peer relations, hostility, risk in postdischarge, and if the intervention has facilitated the process of psychosocial reintegration;Quality of life assessed by the World Health Organization Quality of Life Assessment (WHOQOL-BREF) [25] (T0, T1, T2): to determine if the intervention has improved quality of life—physical, psychological, and independence level—postdischarge;EuroQol Five-Dimensional Questionnaire, Youth Version (EQ-5D-Y) [26] (T0, T1, T2): to determine if this cost-effectiveness tool is appropriate for a fully powered trial along with the intervention fidelity;Data on preliminary resource use will be collected via semistructured interviews with health care staff, young people, and parents/carers. Service use schedules may be developed to assess cost-effectiveness.

